### Sample size and power

The trial aims to recruit a total of *n* = 160 participants. Based on pilot work and previously conducted clinical trials of family-based interventions compared to treatment-as-usual conditions, it has been estimated that it is possible to generate an effect size of *d* = 0.63 in reduction of mental health symptoms, which is equivalent to 14% increase in the odds of remission [45]. Out pilot data also indicates that treatment type by time interaction is able to produce up to 50% remission in depression diagnosis, over and above treatment type. With an alpha of 0.05 and power level of 0.90 for two-tailed tests, intraclass correlation coefficient (ICC) of 0.17 for within therapy group variation (estimated from our pilot data), and estimated 10% of variation in the main outcome accounted for by other variables in the model (treatment arm, time, parental socioeconomic status), the minimum sample size required equates to *n* = 57 per treatment arm. Based on pilot studies, an attrition rate of 20 to 25% is anticipated. Therefore, a minimum of 80 participants into each of the two treatment conditions will be recruited. Comparisons will be undertaken between those who drop out and those who are retained in order to assess for attrition bias.

With respect to our secondary hypotheses, anticipated final sample size of 114 individuals, will also allow us to detect small effect size (d = 0.23) for the treatment arm by time interaction for continuous outcomes, with 90% power and alpha level of 0.05, assuming ICC of 0.20 for within-person (between-assessment) and ICC of 0.07 for within therapy group variation (estimated from our pilot data).

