### Statistical analysis plan

Repeated measures binomial data will be analyzed over three time points using a binary logistic regression within the Generalized Linear Mixed Model (GLMM). The model will be fitted in STATA (xtmelogit). For any continuous-scale data we will use a linear mixed model approach in STATA. For both types of data we will explore variance-covariance structures for the evaluations within an individual. Clinical significance and an index of reliable change will be calculated for each measure using the criteria of Jacobson and Truax [46]. Findings will be analyzed in terms of standardized mean differences and effect sizes achieved will be compared to existing high quality trials to determine relative efficacy of this intervention. Multivariable multilevel models will also explore other covariates on the relationship between treatment arm and study outcomes, with a view to improving the intervention and specifying its ideal target population. Data will be stored in a locked cabinet, and a password protected computer file will contain de-identified (coded) data. A proportion of the data will be double-entered, and range checks will be performed for accuracy checking. Intention-to-treat analysis will be used with the last observation carried forward as a conservative estimate of outcome when data are missing at follow-up.

In addition, analysis of qualitative data from the transcribed interviews of participants who did not take up the option of treatment following intake/assessment, discontinued treatment, or completed treatment will be undertaken. Thematic analysis of participants’ accounts of their experience of the intake/assessment process and reasons for either engaging with or distancing themselves from the treatment offered will be undertaken. Meanings participants assign to the process will also be extracted from the data. Analysis of the data relevant to the phenomena of interest will assist in the identification of barriers to engagement and change for families.

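### Continuous secondary outcomes are tested by an arm-by-time interaction with no described use of baseline; read conventionally, this is unbiased but gives away roughly a quarter to a half of the information

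*Protocol article*

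**What the plan says.** In *Sample size and power*, the paragraph on the secondary hypotheses works from an "anticipated final sample size of 114 individuals" and claims a detectable d of 0.23 "for the treatment arm by time interaction for continuous outcomes", "with 90% power and alpha level of 0.05". It does so "assuming ICC of 0.20 for within-person (between-assessment" correlation, and with a therapy-group ICC of 0.07.

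*Statistical analysis plan* adds only this: "For any continuous-scale data we will use a linear mixed model approach in STATA". It leaves the within-person covariance structure to be explored. The abstract describes multilevel mixed modelling with time-by-treatment effects and random effects for group.

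*Assessments and outcome measures* puts T1 at enrolment, T2 at the end of treatment and T3 three months later; the abstract gives baseline, 8 and 20 weeks. No section says how the T1 value enters the continuous models.

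**The concern.** In a model with arm, time and arm-by-time terms and T1 among the repeated outcomes, the interaction is the between-arm difference in change from T1. That subtracts an estimated baseline difference whose true value under randomisation is zero, so the sampling noise of T1 is added to the treatment effect. The cost is greatest when repeated measurements correlate weakly, and the plan's own value of 0.20 is weak. At that value a change score is noisier than a follow-up score with baseline ignored.

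Secondary hypothesis (a) in *Aims and hypotheses*, that parent and youth mental health and relationships improve more under BEST MOOD, rests mainly on these models. With 114 people analysed, wider standard errors make a real difference harder to show.

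**Working it through.** **Inputs.** From *Sample size and power*: 57 per arm ("the minimum sample size required equates to *n* = 57 per treatment arm", giving the 114), within-person ICC r = 0.20, therapy-group ICC 0.07. From the abstract: equal allocation, one baseline and two follow-ups. Assumed: exchangeable correlation, unit variance, complete data on 114 people, two-sided 5% test (stated for the primary outcome only). Therapy-group size is not stated, so 3 to 10 families is assumed.

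**The plan's own figure.** The detectable effect at 90% power is (1.960 + 1.282) × √(2v/57), where v is the per-person variance of the contrast. Without clustering:
- change to one follow-up, v = 1.60: d = 0.77
- mean of two follow-ups minus baseline, v = 1.20: d = 0.67
- slope per visit, v = (1 − 0.20)/2 = 0.40: d = 0.38
- most favourable variant tried, v = (1 − 0.20)/3 = 0.267: d = 0.31

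The stated 0.23 is not reached. That is a separate matter, and nothing below uses it.

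**Loss without clustering.** The variance of the arm difference is 2v/57, and the loss is 1 − v(common)/v(free).
- One follow-up, free baseline: v = 2(1 − r) = 1.60, variance 0.0561. Common or adjusted baseline: v = 1 − r² = 0.96, variance 0.0337. Loss = 1 − 0.96/1.60 = 40%. Ignoring baseline altogether gives v = 1.00.
- Mean of T2 and T3, free baseline: v = (1 + r)/2 + 1 − 2r = 1.20, variance 0.0421. Common: v = (1 + r)/2 − r² = 0.56, variance 0.0196. Loss = 1 − 0.56/1.20 = 53%.
- Linear slope over weeks 0, 8 and 20: loss 42%, by generalised least squares.

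**What this means for power.** At an illustrative difference of 0.5 SD, unclustered, power is Φ(0.5/√variance − 1.96):
- one follow-up: 56% (free) against 78% (common)
- mean of T2 and T3: 68% against 95%

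**Loss with therapy-group ICC 0.07.** Generalised least squares with a group effect, either present at all three assessments (as a plain random intercept implies) or arising only after T1:

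| Families per group (assumed) | Group effect | One follow-up | Mean of T2 and T3 |
|---|---|---|---|
| 3 | all visits | 35% | 47% |
| 3 | after T1 | 37% | 48% |
| 6 | all visits | 30% | 40% |
| 6 | after T1 | 33% | 41% |
| 10 | all visits | 25% | 33% |
| 10 | after T1 | 29% | 35% |

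The range is therefore about 25-48%.

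**Sensitivity to r, no clustering.** The loss is 25% and 33% at r = 0.5, and 15% and 20% at r = 0.7 (one follow-up and mean respectively).

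**The case against.** The strongest reply is that the protocol never says that the baseline difference is left free. A reader might infer it from the phrase "other variables in the model (treatment arm, time, parental socioeconomic status", but that list belongs to the power paragraph for remission and does not describe the continuous models. A common-baseline model also contains arm-by-T2 and arm-by-T3 terms, so the power statement is compatible with either model, and a separate analysis plan might specify the better one. This stands, and makes the point conditional. It does not remove it: the article names the interaction as the target, describes no use of baseline, and the ordinary fit of such a model is the inefficient one.

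A reader might also take 40-53% as the loss under the plan's assumptions. It is not, because the same sentence gives a therapy-group ICC of 0.07, which lowers the loss. The planned last observation carried forward lowers it too. If 22.5% (the midpoint of the expected 20 to 25% attrition) had T1 only, with equal variances, the T1-to-follow-up correlation would be about 0.775 × 0.20 + 0.225 = 0.38. The unclustered loss would then be about 31% at one visit and 41% for the mean.

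Two stronger inferences fail. The interaction test is not biased or invalid: under randomisation it estimates the right difference and fits the wording of hypothesis (a). Nor do the figures show that real effects will probably be missed: the unclustered power at 0.5 SD is still 56% and 68%.

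Finally, equal T1 means depend on T1 being collected before allocation is known. Table 1 makes the baseline questionnaire an entry requirement, but the enrolment description under *Recruitment* moves from the KID-SCID interview to allocation without placing the questionnaires. This reservation stands and is carried into the fix.

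**Conclusion.** The point holds as a conditional matter of efficiency in the continuous secondary models. If the interaction is fitted in the usual way, about 25-48% of the information is lost at the plan's two ICCs with 3 to 10 families per group. The upper bound of 53% applies only if clustering is ignored. The size depends on the low planning correlation, on an exchangeable structure and on a group size that the article does not give; it shrinks as the correlation rises but does not vanish at the values examined. The primary remission analysis is not affected. The change is worth making because it uses data already collected.

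**What to change.** State in the analysis section how T1 enters the continuous models. Either of these will do:
- model T2 and T3 with the T1 value of the same scale as a covariate; or
- keep T1 as an outcome, constrain both arms to one T1 mean, and include categorical time with arm-by-T2 and arm-by-T3 terms and no arm term at T1.

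In both, keep the therapy-group random effect and report the arm differences at T2 and T3 as the treatment effect.

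Also confirm, and state, that T1 questionnaires are completed before the family knows its allocation. The common-mean constraint relies on this, and a T1 covariate should likewise be measured before allocation is known.

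The cost is a sentence or two of analysis wording and one check of the enrolment sequence. No new data are needed.

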### Statistical analysis plan

Repeated measures binomial data will be analyzed over three time points using a binary logistic regression within the Generalized Linear Mixed Model (GLMM). The model will be fitted in STATA (xtmelogit). For any continuous-scale data we will use a linear mixed model approach in STATA. For both types of data we will explore variance-covariance structures for the evaluations within an individual. Clinical significance and an index of reliable change will be calculated for each measure using the criteria of Jacobson and Truax [46]. Findings will be analyzed in terms of standardized mean differences and effect sizes achieved will be compared to existing high quality trials to determine relative efficacy of this intervention. Multivariable multilevel models will also explore other covariates on the relationship between treatment arm and study outcomes, with a view to improving the intervention and specifying its ideal target population. Data will be stored in a locked cabinet, and a password protected computer file will contain de-identified (coded) data. A proportion of the data will be double-entered, and range checks will be performed for accuracy checking. Intention-to-treat analysis will be used with the last observation carried forward as a conservative estimate of outcome when data are missing at follow-up.

In addition, analysis of qualitative data from the transcribed interviews of participants who did not take up the option of treatment following intake/assessment, discontinued treatment, or completed treatment will be undertaken. Thematic analysis of participants’ accounts of their experience of the intake/assessment process and reasons for either engaging with or distancing themselves from the treatment offered will be undertaken. Meanings participants assign to the process will also be extracted from the data. Analysis of the data relevant to the phenomena of interest will assist in the identification of barriers to engagement and change for families.

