**Methods/Design:**

The Family Options study will determine whether a manualized family based intervention designed to target both individual and family based factors in adolescent depression (BEST MOOD) will be more effective in reducing unipolar depressive disorders than an active (standard practice) control condition consisting of a parenting group using supportive techniques (PAST). The study is a multicenter effectiveness randomized controlled trial. Both interventions are delivered in group format over eight weekly sessions, of two hours per session. We will recruit 160 adolescents (12 to 18 years old) and their families, randomized equally to each treatment condition. Participants will be assessed at baseline, eight weeks and 20 weeks. Assessment of eligibility and primary outcome will be conducted using the KID-SCID structured clinical interview via adolescent and parent self-report. Assessments of family mental health, functioning and therapeutic processes will also be conducted. Data will be analyzed using Multilevel Mixed Modeling accounting for time x treatment effects and random effects for group and family characteristics. This trial is currently recruiting. Challenges in design and implementation to-date are discussed. These include diagnosis and differential diagnosis of mental disorders in the context of adolescent development, non-compliance of adolescents with requirements of assessment, questionnaire completion and treatment attendance, breaking randomization, and measuring the complexity of change in the context of a family-based intervention.

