## Methods/Design

### Overview

The study is a multi-center, double-blind, randomized controlled trial comparing two group interventions: the BEST MOOD program and a treatment-as-usual supportive parenting program known as Parenting Adolescents Support Training (PAST). Both interventions are for families of youth who present with a unipolar mood disorder, here defined as major or minor adolescent depression or dysthymia. In both treatment conditions, families receive eight sessions of treatment delivered over two hours per week. The trial will run across several sites in both metropolitan Melbourne and the regional Victorian city of Geelong. Families will be recruited primarily from the intake service of a large government run mental health service in the eastern region of Melbourne (Eastern Health’s Child and Youth Mental Health Service; CYMHS), but community referrals will also be accepted from schools and community based health and mental health services, and via promotion of the study at community forums. At the completion of the interventions, face-to-face interviews will be conducted to better understand the level of engagement of participants with the treatment following intake/assessment. The aims of the qualitative component of the study are to explore the phenomena of not taking-up treatment, discontinuing treatment after commencement, completing treatment and benefiting from treatment, and the perceived influencing factors on these outcomes.

The primary outcome measure will be rates of remission of depressive disorder (major, minor, or dysthymia), according to a structured diagnostic clinical assessment, utilizing modules from the Structured Clinical Interview for *DSM-IV Childhood Diagnoses* KID-SCID; [28]. The secondary outcome measures will include: adolescent mental health (parent and self-reported), parent mental health, the young person’s level of engagement with mental health services, the parent-child relationship, and the therapist-client working alliance. Psychologists, social workers, and postgraduate psychology students who will be trained and supervised in one of the interventions for an equivalent amount of time, will deliver treatment. Therapists and assessors are blinded to the content of the alternate intervention, and are blinded to whether they are delivering the experimental or control condition in the study.

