### Eligibility criteria

#### Inclusion criteria

Families will be included in the study where there is an adolescent aged 12 to 18 years who is currently presenting with a depressive disorder. Specifically, the young person must, at the time of assessment, meet the criteria for either major depressive disorder, minor depressive disorder, or dysthymic disorder as assessed via current *DSM-IV* criteria.

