### Assessments and outcome measures

The following measures will be administered to assess the previously described study hypotheses across three time points during the trial: enrollment in the trial (T1), completion of treatment (T2), and three months post-treatment completion (T3). To maximize the clinical validity of the outcome evaluations, these assessments will involve both clinician administered and self-report measures. These measures have been chosen based on piloting in previous trials and in terms of minimizing participant burden while maximizing sensitivity to clinical change across key domains.

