#### Youth depressive disorders

The Structured Clinical Interview for *DSM-IV Childhood Diagnoses* (KID-SCID) [28] is a semi-structured instrument designed to generate childhood *Diagnostic and Statistical Manual of Mental Disorders Fourth Edition DSM-IV*[30] diagnoses for clinical research studies. This instrument is modeled on the extensively used adult version (SCID). The modular nature of the KID-SCID permits users to select modules relevant to their research. For the purpose of this trial, modules were selected to enable the differential diagnosis of major depressive disorder, minor depressive disorder and dysthymic disorder. The selected modules were then tailored for use, such that two versions were created: one for completion with the young person, and a brief screening version for completion with a parent/caregiver. The KID-SCID modules will be conducted via telephone with young people, to determine eligibility and to assess the primary study hypothesis.

Modules of the KID-SCID selected for use with young people in this study as follows: Current Major Depressive Episode B1; Current Manic Episode B6; Hypomanic Episode B10; Dysthymia B14; Mood Disorder Due to a General Medical Condition B18; Substance Induced Mood Disorder B20. Modules B6, B10 and B18 and B20 were included as the differential diagnosis of major depressive, minor depressive and dysthymic disorders requires information elicited in the completion of these modules. On the recommendation of KID-SCID developer [name], the research team also used the following modules to the KID-SCID in the current trial: Past Major Depressive Episode, Past Manic Episode, Past Hypomanic Episode, and Major Depressive Disorder E4. These additional modules enable Current Mood Disorder Differential Diagnosis Module E to be completed. Mania, Hypomania and Bipolar Episodes and Disorders were only assessed to the extent that they could be ruled out for the purpose of accurate differential diagnosis of the depressive disorders.

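### The logistic mixed model for remission counts baseline as an outcome visit, although eligibility fixes remission at 0% there, so the time-by-treatment term is a poor basis for the primary test

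*Protocol article*

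**What the plan says.** The Overview defines the endpoint: "The primary outcome measure will be rates of remission of depressive disorder (major, minor, or dysthymia"). The Statistical analysis plan section gives the model: "Repeated measures binomial data will be analyzed over three time points using a binary logistic regression within the Generalized Linear Mixed Model (GLMM"), fitted with xtmelogit. Assessments and outcome measures defines the visits as "enrollment in the trial (T1), completion of treatment (T2), and three months post-treatment completion (T3"), and the abstract gives the timing: "Participants will be assessed at baseline, eight weeks and 20 weeks".

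Under Inclusion criteria the young person must, when assessed, "meet the criteria for either major depressive disorder, minor depressive disorder, or dysthymic disorder as assessed via current" DSM-IV criteria. Youth depressive disorders gives one instrument both jobs: "The KID-SCID modules will be conducted via telephone with young people, to determine eligibility and to assess the primary study hypothesis". The Reimbursement section confirms that the interview is held at all three time points.

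On the effect of interest, the abstract describes mixed modelling "accounting for time x treatment effects and random effects for group and family characteristics". The Sample size and power section credits the pilot remission result to the interaction of treatment with time, and lists treatment arm and time among the variables in the model. Nowhere does the article say whether time is categorical or linear, that T1 is left out as a response, or that the arms are held equal at T1.

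**The concern.** Baseline is a useful response for a continuous score, because it varies between patients and anchors change. Here the response at baseline is a constant set by the entry rule. A logistic model has no finite log-odds for a cell with no events, and an interaction measured from that cell inherits the problem. If time is instead forced onto a straight line, the line must start from an artificial extreme, and its slope no longer isolates the difference in remission between arms.

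At stake is the test of the primary hypothesis. An analyst who reads the interaction as the deciding coefficient will get either an undefined number or a test with little chance of detecting the planned effect. The analyst would then have to choose another contrast with the data in hand.

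**Working it through.** **Inputs from the article.** Visits at 0, 8 and 20 weeks (abstract). Remission at T1 of 0% in both arms (Inclusion criteria; Youth depressive disorders). From Sample size and power: d = 0.63, two-sided alpha 0.05, power 0.90, 10% of variance explained, therapy-group ICC 0.17, 57 per arm.

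**Assumptions, because the article gives no arm-specific remission rates.** Control remission 10–30% at T2 and 30–50% at T3; latent T2–T3 correlation 0.2 or 0.5; no therapy-group clustering, which flatters every model.

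**1. The plan's own figure.** n = 2 × ((1.96 + 1.2816)/0.63)² = 52.9, or 54 per arm with the t distribution. Then 54 × 0.90 = 48.6. The design effect is 1 + (m − 1) × 0.17 for group size m. For m = 2: 48.6 × 1.17 = 56.9, which matches 57. For m = 6, 8 or 10 it gives about 90, 106 or 123. Group size is not stated, so 57 can be neither confirmed nor refuted. I take it as given.

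**2. Effect on the odds scale.** exp(0.63 × π/√3) = exp(1.143) = 3.14. A control rate of 30% has odds 0.429; 0.429 × 3.14 = 1.344, or 57.3% remission. (The article equates d = 0.63 with a 14% rise in odds. That is a separate matter, and I use the conversion from d.)

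**3. Categorical time.** Relative to T1, the interaction at visit k is

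[logit p(BEST, k) − logit p(PAST, k)] − [logit p(BEST, T1) − logit p(PAST, T1)].

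With p = 0 in both arms at T1, the second bracket is (−∞) − (−∞). Each cell contributes variance 1/(n p (1 − p)), which is unbounded as p approaches 0. In a logistic fit with 57 of 57 depressed at T1 in each arm, the interaction's standard error was 37 after 10 iterations, 5,476 after 20 and 813,127 after 30. The likelihood ratio for the interaction was 0.00 even with 30% v 57% remission at both follow-ups: the arm main effect absorbs the difference, and T1 puts no constraint on it. All that the interaction can still test is whether the arm effect differs between T2 and T3, with power of about 5% for a sustained effect.

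**4. Linear time with an arm main effect.** Random-intercept logistic model, 57 per arm, 500 simulated trials per scenario, time coded 0/1/2 or 0/8/20 weeks, likelihood-ratio test. The comparator is a random-intercept model on T2 and T3 only, testing an arm effect common to both visits.

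| Scenario (control remission T2/T3) | Interaction, three visits | Arm effect, T2 and T3 only |
|---|---|---|
| OR 3.14 at both (30/30%) | 9–11% | 95–99% |
| OR 3.14 at both (20/30%) | 4–6% | 94–98% |
| OR 3.14 at both (30/50%) | 15–20% | 94–97% |
| OR growing (20/30% or 10/40%) | 17–27% | 75–83% |
| OR 3.14 at T3 only (20/30%) | 41–54% | 57–61% |

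In the growing case the OR is about 1.77 at T2 (the square root of 3.14) at most, rising to 3.14 at T3; the simulated T2 rates of 28.3% v 20% and 14.9% v 10% correspond to an OR of 1.58. With no effect, the interaction rejected in 0.2–0.6% of trials, so the test is far more conservative than its nominal 5%.

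The reason shows in an expected dataset (30% v 57.3% at both visits, correlation 0.5, time 0/1/2). The arm main effect takes part of the difference, leaving a likelihood ratio of 1.4 for the interaction. The arm effect in the T2/T3 model has 13.0.

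**5. Closed-form check at one follow-up.** SE = √(1/(57 × 0.30 × 0.70) + 1/(57 × 0.573 × 0.427)) = 0.394. Then 1.143/0.394 = 2.90, and power is Φ(2.90 − 1.96), about 83%. Simulated power for T3 alone was 81–86%.

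**The case against.** The strongest reply is that the article never names the interaction as the deciding test. The primary hypothesis is a comparison of remission between arms. The time-by-treatment wording sits in an abstract sentence covering all data and in a remark about the pilot; the sample size section sets that interaction as a target only for continuous outcomes. With categorical time, T1 drops out of the likelihood: in one simulated dataset fitted with and without T1, the arm log-odds ratios at T2 and T3 agreed both ways (2.507 and 0.730). All of this stands. A reader might infer that the trial cannot answer its primary question, or that the software output would be meaningless throughout. The documents do not support either inference: only coefficients referenced to T1 are undefined.

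A linear model without the arm main effect, so that the arms are equal at T1, had 83–97% power. That also stands, but the article lists treatment arm in the model and states no such constraint.

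A reader might patch the empty cells by adding 0.5 and report about 8% power. That figure is set almost wholly by the added constant and is not the planned model. Nor does the article say that T2 and T3 are each tested at 5%, so an inflated error rate cannot be charged to it.

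Finally, a condensed article may leave time coding and the exact contrast to a fuller plan. The absence of those details is not the fault here. The fault is that a stated model over three visits conflicts with a stated entry rule.

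**Conclusion.** Wrong as written for the binary primary outcome. T1 carries no information on the treatment effect. The time-by-treatment term has no finite estimate relative to baseline if time is categorical; that conclusion needs no assumed remission rate. If time is linear with an arm main effect, power was well below 90% in every scenario tried: roughly 4–20% for an OR of about 3.14 sustained at both follow-ups, and up to about 54% if the effect appears only at T3. Those figures depend on the assumed remission rates and correlations, on 57 per arm, and on leaving out therapy-group clustering. That the interaction is the intended test is inferred from the abstract and the sample size section. The primary question remains answerable through an arm contrast at follow-up, provided that the plan places the test there.

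**What to change.** For remission, use only T2 and T3 as responses: treatment, visit, treatment by visit, with random effects for adolescent and therapy group. Let baseline measures enter only as covariates. Before unblinding, name one primary contrast, either the treatment odds ratio at one stated follow-up or its average over T2 and T3, and make the other secondary. The choice matters: if the effect appears only at T3, the common-effect test had 57–61% power against about 84–86% for T3 alone, whereas the common-effect test does better when the effect is sustained. Keep the three-time-point model for the continuous outcomes. The cost is analysis wording only, with no new data, visits or patients.

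### The primary remission model is tied to xtmelogit, whose default z test of the between-arm contrast is too liberal if therapy groups are few: about 6–10% false positives instead of 5% with an assumed 10–26 groups

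*Protocol article*

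**What the plan says.** The protocol article, section Statistical analysis plan, sets a binary logistic mixed model over three time points for the binary data and names the software: "The model will be fitted in STATA (xtmelogit". It gives no test statistic, reference distribution or degrees of freedom.

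The abstract adds that the modelling has time-by-treatment effects and "random effects for group and family characteristics". The section Sample size and power sets the error rates, "With an alpha of 0.05 and power level of 0.90 for two-tailed tests", and the clustering it expects, "intraclass correlation coefficient (ICC) of 0.17 for within therapy group variation (estimated from our pilot data".

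The abstract and the two intervention sections describe both treatments as group programmes, so each therapy group lies wholly within one arm. No section gives the number or size of the groups. The primary hypothesis (Aims and hypotheses) is a higher remission rate under BEST MOOD than under PAST. The inclusion criteria require a current depressive disorder at assessment.

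**The concern.** Where whole therapy groups belong to one arm and outcomes within a group are correlated, the groups carry much of the information on the arm difference. With few groups, two things go wrong in a default maximum-likelihood fit. The group variance tends to be estimated too low, and the Wald statistic is compared with 1.96 although the between-group variation rests on few degrees of freedom. Both make the p-value too small and the interval too narrow, even when the group random effect is correctly included. A primary p-value between about 0.03 and 0.05 could then be reported as meeting the two-sided 5% level when it does not.

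**Working it through.** **The plan's own figure.** The article states alpha 0.05 and reports no operating characteristic for the fitted test, so there is no stated error rate to reproduce. The nearest computed figure is "the minimum sample size required equates to *n* = 57 per treatment arm". It does not reveal the group size:

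- For d = 0.63 at 90% power, n = 2(1.960 + 1.282)²/0.63² = 53 per arm.
- Multiplying by 0.9 for the 10% explained variation gives 48.
- With the design effect 1 + (m − 1)0.17, a total of 57 needs only m ≈ 1.5 (from 53) or m ≈ 2.2 (from 48) participants per group.

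The number of groups therefore has to be assumed.

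**Inputs from the article.** Two-sided alpha 0.05, therapy-group ICC 0.17, 160 recruited, 114 expected at the end.

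**Assumed inputs.**
- Number of groups G: 160/16 = 10 up to 160/6 ≈ 26, with 160/4 = 40 as an outer case.
- ICC read on the logit scale: group variance = 0.17/0.83 × π²/3 = 0.67, so SD 0.82.
- Remission of 40% in both arms (no treatment effect).
- One post-baseline outcome per youth.

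**Step 1, approximation.** The two-sided tail beyond 1.96 of a t distribution with G − 2 degrees of freedom.

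**Step 2, simulation.** 3,000 null trials per setting. A random-intercept logistic model was fitted by maximum likelihood (Gauss–Hermite quadrature), and the Wald statistic for arm was compared with 1.96 and with the t critical value on G − 2 df. Simulation standard error is about 0.4–0.5 points.

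| G | t tail beyond 1.96 | z, n = 114 | z, n = 160 | t(G − 2), n = 114 | t(G − 2), n = 160 |
|---|---|---|---|---|---|
| 10 | 8.6% | 10.0% | 10.1% | 5.5% | 6.1% |
| 14 | 7.4% | 8.0% | 8.1% | 5.6% | 5.2% |
| 20 | 6.6% | 6.2% | 8.0% | 4.2% | 6.0% |
| 26 | 6.2% | 5.8% | 6.4% | 4.8% | 5.0% |

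**Step 3, sensitivity.**
- A further set at ICC 0.17 gave 10.2%, 6.6%, 7.2%, 6.4% and 5.6% for 10, 14, 20, 26 and 40 groups with z, and 4.9–5.8% with t. The t-tail approximation for 40 groups is 5.7%.
- With 37% remission (also assumed; 1,500 trials per setting) and 10 to 26 groups of 12 down to 6, z gave 6.0–8.8% and t gave 4.5–5.8%. A group-level t-test gave 4.7–5.3%.
- A likelihood-ratio test at ICC 0.17 gave 5.8–8.2%, so choosing it instead does not remove the problem.
- At ICC 0.07, which the article gives for continuous secondary outcomes, z gave 5.0–9.3%.

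**Step 4, other contrasts.** Two post-baseline occasions, n = 114, ICC 0.17, 1,000 trials per setting, z test, random intercept fitted.
- Group effect constant over time: arm-by-time 4.9% (10 groups) and 4.2% (26 groups); arm effect at the first occasion 8.6% and 4.9%.
- Group effect different at each occasion: arm-by-time 19.8% and 12.5%.

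**Interval width.** 2.306/1.960 = 1.18 for 10 groups (8 df); 2.064/1.960 = 1.05 for 26 groups (24 df).

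**The case against.** The strongest reply is that the article names a fitting command and not a test. Wald, likelihood-ratio or small-sample inference is commonly left to a separate analysis plan, which is not shown and may already deal with this. That stands as a limit: the z test is inferred from the command's default. It does not dispose of the point, because the article fixes the estimator, and an analyst who follows it as written obtains z-based p-values.

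Second, the number of groups, the remission rate and the scale of the ICC are assumptions. This also stands. At 26 groups the excess is small: 5.8% has a 95% simulation range of about 4.9–6.6%, and one two-occasion run gave 4.9%.

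Third, the planned model covers three time points and includes time-by-treatment effects, and an arm-by-time test with constant group effects shows no inflation. That result concerns whether the arm difference changes between the two follow-ups. The primary hypothesis is different. Every youth is depressed at entry, so baseline remission is zero in both arms, and the evidence on remission comes from post-baseline rates compared between arm-specific groups.

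A reader might infer that the trial's actual false-positive rate is 6–10%, or that the protocol prescribes a z test. The documents support neither. A reader might also extend the criticism to the continuous outcomes, but the article says only that a linear mixed model will be used and does not specify maximum likelihood for them.

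**Conclusion.** The point holds as a conditional risk. If 160 families form about 10 to 26 therapy groups, a default z test of the between-arm post-baseline remission contrast has a type I error of about 6–10% at the stated ICC of 0.17, and about 5.6% with 40 groups. This rests on a group random intercept, the ICC taken on the logit scale, an assumed null remission rate near 40%, and a model simpler than the planned three-time-point one.

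The range does not cover other contrasts. For arm-by-time between the two follow-ups, the size depends on whether group effects change over time, and it can lie at about 5% or well above 10%. The point deserves a change before analysis because the estimator is named, the clustering is expected by the authors, and the remedy is cheap.

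**What to change.** Add to the section Statistical analysis plan that the treatment test and 95% confidence interval for remission use a t distribution with (number of therapy groups minus 2) degrees of freedom, and that a group-level t-test comparing remission proportions between arms is reported as a check. State the expected number and size of therapy groups, so that a reader can judge how much the choice matters. If a separate analysis plan already contains this, a cross-reference is enough.

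The cost is wording only, with no extra participants or data. Confidence intervals become about 5% wider with 26 groups and 18% wider with 10, with some loss of nominal power. For the continuous outcomes, REML with Kenward–Roger or the same between-group degrees of freedom is an optional refinement.
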